## Abstract

**Background:**

Continuous monitoring of vital signs and other biological signals in the Neonatal Intensive Care Unit (NICU) requires sensors connected to the bedside monitors by wires and cables. This monitoring system presents challenges such as risks for skin damage or infection, possibility of tangling around the patient body, or damage of the wires, which may complicate routine care. Furthermore, the presence of cables and wires can act as a barrier for parent-infant interactions and skin to skin contact. This study will investigate the use of a new wireless sensor for routine vital monitoring in the NICU.

**Methods:**

Forty-eight neonates will be recruited from the Montreal Children’s Hospital NICU. The primary outcome is to evaluate the feasibility, safety, and accuracy of a wireless monitoring technology called ANNE^®^ One (Sibel Health, Niles, MI, USA). The study will be conducted in 2 phases where physiological signals will be acquired from the standard monitoring system and the new wireless monitoring system simultaneously. In phase 1, participants will be monitored for 8 h, on four consecutive days, and the following signals will be obtained: heart rate, respiratory rate, oxygen saturation and skin temperature. In phase 2, the same signals will be recorded, but for a period of 96 consecutive hours. Safety and feasibility of the wireless devices will be assessed. Analyses of device accuracy and performance will be accomplished offline by the biomedical engineering team.

**Conclusion:**

This study will evaluate feasibility, safety, and accuracy of a new wireless monitoring technology in neonates treated in the NICU.

## Introduction

### Background

In Canada, approximately 11.1% of newborns require admission to the Neonatal Intensive Care Unit (NICU) after birth (Fallah et al., 2011). Common causes for admission are prematurity, low birth weight, respiratory distress syndrome, apnea of prematurity, and hypoglycemia (Gallacher, Hart & Kotecha, 2016). NICU patients require around the clock care and continuous monitoring of their vital signs including heart rate (HR), temperature, oxygen saturation (SpO_2_), and respiratory rate (RR). Monitoring of these signs is essential for providing effective care.

Current standard monitoring technologies involve sensors that are applied to the body and connected to bedside monitors using wires and cables. Heart rate is measured *via* small electrodes connected *via* wires and cables to the bedside monitor that continuously displays both electrocardiogram (ECG) tracings and average HR. Temperature is monitored *via* a probe placed at the axilla and oxygen saturation (SpO_2_) *via* a sensor placed on the extremities (fingers, hand, wrists, or foot) with the values and signal tracing displayed on the bedside monitor. Finally, respiratory rate is measured *via* thoracic impedance using the same sensors and wires as the ECG (Kumar et al., 2019). Thus, current standard of care is a wired monitoring system involving multiple sensors applied to the skin with long wires and cables connected to the bedside monitors.

The presence of multiple wires poses several hindrances. First, wires can act as a barrier to parent-infant bonding (Al Maghaireh et al., 2016; Jämsä & Jämsä, 1998; Lantz & Ottosson, 2012). In a systematic review, parents expressed that the complex wired system in their infant’s crib made them reluctant to hold the baby. Bonding is important for the parent’s emotional health and is also associated with better outcomes for the infants (Mehrpisheh et al., 2022). Indeed, skin-to-skin contact or Kangaroo-care, has been linked to pain reduction, and better physiological and behavioral outcomes (Conde-Agudelo, Belizán & Diaz-Rossello, 2011). Second, the multiple wires can tangle and restrict the baby’s natural movement leading to discomfort or touch the floor, increasing the risk of nosocomial infections (Bonner et al., 2017; Russotto et al., 2015). To avoid tangling and movement restriction, sensors are often removed and reapplied which can cause harm to the sensitive neonatal skin and disturb infants’ rest, both contributing to pain and distress (Chen et al., 2009). Nurses reported that any technology able to reduce handling of premature babies would significantly improve patient outcomes (Bonner et al., 2017).

Interestingly, monitoring technology in neonatal care has undergone little change in the last five decades since the addition of pulse oximetry as standard of care (Xu et al., 2021). Despite witnessing rapid technological advances in smart monitoring and wearable devices across industries, the hospital sector has lagged in implementing these devices (Lewy, 2015; De Georgia et al., 2015). However, in recent years there have been interesting developments on wireless and wearable technologies for infant monitoring. Some consumer technologies such as the Owlet Smart Sock, MonBaby, and Lumi have been designed for neonates but are not FDA-cleared Class III medical devices (Al Maghaireh et al., 2016; Hewitt et al., 2019; Roh, 2021). While these devices have the potential for hospital monitoring, they must meet rigorous criteria for medical devices, and preliminary studies have shown limitations in their accuracy (Bonafide et al., 2018; Bonafide, Jamison & Foglia, 2017).

Recently, a vital sign monitoring system called ANNE^®^ Monitoring System was developed that uses small, light wireless sensors attached to the newborn’s skin (Chung et al., 2019). A pilot project including 21 neonates with gestational age between 28 weeks to full term, demonstrated good safety and efficacy in detecting heart rate, respiratory rate, temperature, and SpO_2_ when compared to current standards of care, over a 5-min period. In a second study, investigators strengthened the mechanical properties of the sensors, and examined different power-support schemes, including modular primary batteries, embedded secondary batteries, and wireless power transfer (Chung et al., 2020). Additional features such as the continuous capture of body orientation and movements and acoustic signals of respiratory and cardiac activity *via* tri-axial accelerometers were added. This updated version was tested on 50 NICU & Pediatric Intensive Care Unit (PICU) patients, ranging from extremely preterm to term patients. Results showed that all signals obtained from wireless technologies were within FDA requirements for agreement with the standard measures; there were no negative skin reactions; and heat generation was negligible. However, the strength of this analysis was limited by the small sample sizes. Comparative analysis of signals was only reported for a select number of patients. In the case of HR, SpO_2_, and temperature, comparative analysis was only reported in three patients, while for RR, comparative analysis was only reported in six patients. Skin condition and heat generation was assessed and reported for all patients. In both preliminary studies the investigators demonstrated reliable, safe wireless data transmission, real-time signal processing and data display. Therefore, in this study we will test the feasibility, safety, and accuracy of ANNE^®^ One for longer periods of monitoring in a larger number of neonates, of variable gestational ages and clinical conditions, receiving care in the NICU.

### Study objectives

The objectives of the study are to: (1) demonstrate the feasibility of continuous wireless monitoring in term and preterm infants with variable degrees of maturation and clinical stability in the NICU; (2) assess safety of using a special wireless monitoring system in neonates; and (3) evaluate the accuracy, signal coverage and quality of the proposed wireless technology as compared to standard monitoring technology in the NICU.

## Materials and Methods

### Study design

This is a single center prospective observational study aimed at determining the safety, feasibility, and accuracy of wireless monitoring in the Neonatal Intensive Care Unit. This study design conforms to recommendations by the Standard Protocol Items: Recommendations for Interventional Trials (SPIRIT) (see Additional File 1).

### Study setting

This study will be conducted in the NICU at the Montreal Children’s Hospital.

### Research ethics approval

This study has been reviewed and approved by the Pediatric (PED) panel of the Research Ethics Board of MUHC (#2022-7704). The study was also registered on clinicaltrials.gov on July 8, 2021 (NCT04956354). Any changes in protocol modifications will be communicated to the Research Ethics Board of the MUHC by the principal investigators.

### Consent to participate

All participants will provide article consent which will be obtained by member of research team prior to taking part in the study. Any modifications to the protocol which may impact the study’s intervention, target enrollment group, and outcomes will result in a formal amendment to the protocol. All amendments will be submitted and reviewed by the Research Ethics Board for approval and reflected in the registration on clinicaltrials.gov.

### Eligibility criteria

Three different age groups will be included: Group 1 = term infants (37^+0^ to 40^+6^ weeks); Group 2 = preterm infants with postmenstrual ages 28^+0^ to 36^+6^ weeks, and Group 3 = extremely preterm infants with postmenstrual ages 23^+0^ to 27^+6^ weeks. Groups were designed by neonatologist to reflect a variety of common clinical situations encountered in the NICU. Each age group will consist of a variety of subgroups based on different clinical criteria for inclusion (Table 1). Infants with congenital anomalies and surgical conditions (gastroschisis, omphalocele, congenital diaphragmatic hernia), congenital heart disorders, will be excluded to reduce interference of research with care, and reduce interruptions in data collection. Additionally, infants congenital skin infections or known conditions with fragile skin (such as *epidermolysis bullosa*) will be excluded to prevent additional discomfort or complications associated with adhesives. See Fig. 1 for enrollment plan.

**Table 1 table-1:** Study population characteristics.

Groups	Clinical characteristics	Phase 1 (*n* = 24)	Phase 2 (*n* = 24)
Group 1—Term infants with postmenstrual ages at enrollment of 37–42 weeks’	***A:*** healthy* infants in room air at enrollment (*N* = 6)	3	3
	***B:*** infants with perinatal asphyxia undergoing therapeutic hypothermia at enrollment (*N* = 6)	3	3
Group 2—Preterm infants with postmenstrual ages at enrollment of 28^+0^ to 36^+6^ weeks	***C:*** healthy* infants in room air at enrollment (*N* = 6)	3	3
	***D:*** infants on continuous positive airway pressure at enrollment (*N* = 6)	3	3
Group 3—Preterm infants with postmenstrual ages at enrollment of 23^+0^ to 27^+6^ weeks	***E:*** infants on conventional mechanical ventilation at enrollment (*N* = 6)	3	3
	***F:*** infants on high frequency ventilation at enrollment (*N* = 6)	3	3
	***G***: infants on nasal intermittent positive end expiratory pressure at enrollment (*N* = 6)	3	3
	***H***: infants on continuous positive airway pressure at enrollment (*N* = 6)	3	3
**Total:**		24	24

**Note:**

* Healthy in this study is defined as babies in room air, not requiring respiratory support such as high flow nasal canula (HFNC), continuous positive airway pressure (CPAP), Nasal intermittent positive pressure ventilation (NIPPV), conventional mechanical ventilation (CMV), no evidence of major congenital anomalies, neurological problems, necrotizing enterocolitis (NEC) or infection. The reason baby is admitted in the NICU will be recorded.

**Figure 1 fig-1:**
[figure not shown]
Study enrollment flow diagram. Flow chart describing the flow of patient recruitment for this study.

### Interventions

#### Study equipment

This project will use the ANNE^®^ One from Sibel Health (Fig. 2). ANNE^®^ is a wireless vital sign monitoring system that uses soft, flexible, skin-mountable biosensors (ANNE^®^ Chest and ANNE^®^ Limb) enabled with Bluetooth^®^ 5 encrypted data communication to a mobile device application. It consists of two units which together obtain heart rate, respiratory rate, temperature, oxygen saturation, and movement data. The chest unit is secured *via* a hydrogel adhesive, and the limb unit *via* a fabric strap. These two units are rechargeable, and on full charge have a 36-h battery life. Devices take approximately 3 h to fully recharge.

**Figure 3 fig-3:**
[figure not shown]
ANNE^®^ one wireless sensors. Two devices comprising ANNE^®^ One monitoring system and signals to be acquired by the chest and limb sensors. ANNE^®^ One chest obtains electrocardiography, accelerometry, and temperature. ANNE^®^ One limb: obtains photoplethysmography, temperature. Image provided and approved for publication by Sibel Inc. (Chicago, IL, USA).

Sensor 1—A chest unit (ANNE^®^ Chest) with embedded battery, ECG electrodes, clinical grade thermometer, and a three-axis accelerometer that captures the following signals: electrocardiography (ECG), temperature, and chest wall movements. The sensor will be placed in the middle of the infant’s chest.

Sensor 2 (phases 1 and 2)—A limb unit (ANNE^®^ Limb) with embedded battery, clinical grade thermometer, and two LEDs along with a photodiode that capture photoplethysmogram (PPG) at each wavelength of light, from which the SpO_2_ is calculated. The sensor will be placed on either ankle-to-base of the foot or the wrist-to-hand, with rotations done as per standard of care (every 4 h for preterm infants and every 12 h for term infants).

Sensor 3 (phase 2 only) An abdominal unit (ANNE^®^ Chest) with embedded battery, sensors, and a three-axis accelerometer that captures the following signals: electrocardiography (ECG), temperature, and abdominal wall movements. Only signals of abdominal wall movements will be sampled. The sensor will be placed above the umbilical line.

During the monitoring periods a Biosensors Data Aggregation and Synchronization (BioDASh) system developed by iKinesia Inc (Montreal, Quebec, Canada) for this study will simultaneously record the vital signals from both systems: wired and wireless. The only vital sign recording that will not be recorded continuously by BioDash is the standard temperature which is recorded using a clinical grade handheld thermometer or by a temperature sensor adhesive connected to the incubator. The reasons for this are: (a) temperature is not continuously recorded in all patients in the NICU and (b) BioDash is not able to connect and record signals from to the incubator.

The BioDash application will be running on the study laptop attached to the study cart in the patient room and display all signals in real time, store them, as well as allow team to make live annotations to data. A list of standardized annotations was created to add more details to recorded data. The full list of standardized annotations is provided in Table S1. Additionally, BioDash’s has a visual display providing information about serial number of paired sensors, battery level of the wireless sensors, electrodes contact with the skin, and strength of connection between sensors and the tablet.

In addition, photographs of the skin at the site of sensors placement will be taken before placement and after removal.

#### Study phases

**Phase 1**: Clinical and physiological data will be continuously acquired for 8 h during daytime, for 4 consecutive days. The wireless sensors will be visually assessed and disinfected using 70% isopropyl wipes prior to placement and following device removal each day of the study. Sensors will be disinfected using the same solution at the end of the study.

The ECG and SpO_2_ leads will be connected to a Philips Intellivue monitor (Intellivue MX450; Philips Healthcare, Best, Netherlands) to capture ECG and HR, PPG, SpO_2_, and respiratory waveform and rate data to be displayed and exported in real-time using a direct cable connected to a personal laptop computer *via* MediCollector software (Boston, MA, USA). At the beginning of each day, ANNE^®^ sensors are selected for pairing by the researcher with the BioDash recording system based on serial number displayed both on tablet and devices. Data from the paired ANNE^®^ sensors will be transferred *via* Bluetooth to a study tablet which will simultaneously send this data to the study laptop. The following waveforms and vital signs from both systems (*via* Philips Intellievue MX450) and ANNE^®^ sensors will be recorded: ECG and heart rate, PPG, SpO_2_, respiratory waveform and respiratory rate signals. In addition, body temperature will be recorded from ANNE^®^ sensors only. The BioDASh application running on the study laptop will stream, display, and log data in real-time. In addition, photographs of the skin at the site of placement of the sensors will be taken at baseline, time of device removal.

**Phase 2**: Clinical and physiological data will be acquired for 96 consecutive hours. The sensors will be replaced every 24 h or whenever low battery is detected. The wireless sensors will be visually assessed and disinfected using 70% isopropyl wipes prior to initial device placement, at each replacement, and following device removal at the end of the study. The same signals as in Phase I will be recorded by the BioDash Application.

In phase 2, respiration will also be recorded using uncalibrated respiratory inductive plethysmography (RIP—Respitrace QDC^®^; Viasys^®^ Healthcare, Conshohocken, PA, USA), with the belts applied at the level of the chest and abdomen, for a period of 2 to 3 continuous hours each day, to measure chest and abdominal wall movements, respectively. The Respitrac^®^ signals will also be displayed in real-time on the BioDASh application using the National Instruments (NI) data acquisition system (National Instruments, Austin, TX, USA) *via* Bayonet Neil-Concelman (BNC) cables to an NI (National Instruments, Austin, TX, USA) data acquisition system (NI USB-6212 BNC). Respitrace^®^ signals will be displayed and logged in real-time on the study laptop by the BioDASh application. Acquired signals from all three devices will be stored by BioDASh and used for offline analysis. In addition, photographs of the skin at the site of placement of the sensors will be taken at baseline, time of device replacement, and 96 h.

### Outcomes

#### Objective 1. Demonstrate the feasibility of continuous wireless monitoring in term and preterm infants with variable degrees of maturation and acuity in the NICU

Feasibility will be assessed by reporting challenges associated with sensor placement and removal, and acceptability of the continuous wireless monitoring system by parents and bedside nurses.

Data Annotations: To assess the feasibility of using these wireless sensors the number of times a sensor was readjusted, removed, or replaced will be collected *via* the live annotations added in BioDash by the researchers. Researchers may also add annotations related to difficulties applying and removing the sensors.

Parent and Nurse Survey: The research team will also approach parents and bedside nurses at the end of the 4 days with a short, anonymous survey to obtain perceptions about the wireless wearable devices (Additional File 2). The survey consists of three questions:
Were you satisfied with the wireless sensors placed on your baby during their participation in this project? (Score 0—not satisfied at all to 10—very satisfied)What are things you liked about the wireless sensors?Did you encounter any problems with the wireless sensors? If yes, please specify.

#### Objective 2. Assess safety of using a special wireless monitoring system in neonates

Safety will be assessed by reporting any adverse skin reactions to sensors as well as evaluating pain at the time of device removal.

Skin Evaluation: Prior to device placement and following removal, photographs of the skin at the site of device placement will be taken. A board-certified dermatologist will evaluate these pictures and score according to the Neonatal Skin Condition Score (NSCS). The NSCS has been widely validated for assessment of skin conditions in neonates (Lund & Osborne, 2004) and consists of three items graded from 0 to 3 with final scores ranging from 3 (perfect) to 9 (worse).

Neonatal Infant Pain Scale: Upon sensors removal, the researcher will complete the Neonatal Infant Pain Scale (NIPS) to ensure that removal of adhesive does not cause discomfort to the patient. This scale has been widely validated for the assessment of acute pain in neonates (Witt et al., 2016) and consists of six items: facial expressions, cry, breathing patters, positioning of arms and legs, and state of arousal. All items except cry, which is scored from 0 to 2, are scored from 0 to 1 based. Scores range from 0 to 7, with scores greater than 3 indicating pain.

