#### Objective 2: Assess safety of using a special wireless monitoring system in neonates

A dermatologist will score photographs of the patient skin prior to device placement, and following device removal, using Neonatal Skin Condition Score (NSCS) (Lund & Osborne, 2004). Before and after photograph pairs will be randomized prior to evaluation NSCS scores can range from 3 = intact condition skin to 9 = very poor condition skin. Any change of score from baseline to device removal (
}{}${{\rm \Delta}_{NSCS}} = NSC{S_{removal}} - NSC{S_{baseline}})$ will be reported as part of the sensor safety analysis. A one sample Wilcoxon test will be performed to determine if the mean change NSCS scores (
}{}$\overline {{{\rm \Delta}_{NSCS}}} )\;$are statistically different than 0 indicating no change in score from baseline.

Safety will also be assessed by evaluating the subjective pain scores obtained with the NIPS results. The average score will be reported, and any score of 3 or greater will be counted as indicative of pain. The total number of scores of 3 or more will be reported. Additionally, a one sample Wilcoxon test will be performed to determine if the average obtained NIPS score is below 3.

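### Pain is scored only at sensor removal and analysed as an absolute value, so a raised score cannot be attributed to removing the adhesive

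*Protocol article*

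**What the plan says.** In the protocol article, Outcomes, Objective 2, safety is to cover skin reactions and "evaluating pain at the time of device removal". The timing and purpose of the pain score are given as "Upon sensors removal, the researcher will complete the Neonatal Infant Pain Scale (NIPS) to ensure that removal of adhesive does not cause discomfort". The same section sets the scale and its cut-off: "Scores range from 0 to 7, with scores greater than 3 indicating pain".

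Statistical methods, Objective 2 gives the analysis. The average is reported, and "any score of 3 or greater will be counted as indicative of pain". Then "The total number of scores of 3 or more will be reported", and "a one sample Wilcoxon test will be performed to determine if the average obtained NIPS score is below 3". All of these use the score at removal by itself.

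The skin score in the same objective is handled differently. It has a baseline: "Prior to device placement and following removal, photographs of the skin at the site of device placement will be taken". It is analysed as a difference, removal minus baseline: "Any change of score from baseline to device removal" is to be reported and the mean change tested against zero.

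No NIPS score before removal is described anywhere in the article. The participant timeline (Table 4) and the description of the data collection forms do not mention NIPS. The forms themselves are supplementary and not shown.

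**The concern.** The stated purpose is to show that taking the adhesive off does not cause discomfort. That is a statement about change, and a single score after the event does not measure change.

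The study population makes this more than a formality. NIPS includes breathing pattern, cry and state of arousal. By Table 1, subgroups D to H (5 × 6 = 30 infants) are on respiratory support and subgroup B (6 infants) is undergoing therapeutic hypothermia. So 36 of 48 infants (75%) are in states where some items may be altered before anyone touches the sensor. The section on study equipment also says that sensors come off and go back on around routine care, so other handling can coincide with a removal.

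At stake is the reading of one of the two safety measures. Background distress could be reported as sensor pain. Equally, a real rise caused by removal could go unseen because it stays under the cut-off.

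**Working it through.** The article gives no figure to reproduce: the sample of 48 is a convenience sample and the pain outcome has no power statement. The check is a comparison of the two safety measures, followed by an illustration on assumed inputs.

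**1. The two safety measures side by side**

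| | Skin (NSCS) | Pain (NIPS) |
|---|---|---|
| Before | Photographs before placement | None described |
| After | Photographs after removal | Score at removal |
| Quantity analysed | Removal minus baseline | Absolute score |
| Test | Wilcoxon on the change, against 0 | Wilcoxon on the score, against 3 |

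**2. Planned removal occasions.** Phase 1 has daily removal over 4 days: 24 × 4 = 96. Phase 2 has replacement at least every 24 h over 96 h: 24 × 4 = 96. The total is at least 192 scheduled occasions. The article does not say how many of these will have a NIPS score.

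**3. What a count of raised scores can show.** Let b be the share already at 3 or more just before removal, and a the share of the remainder pushed to 3 or more by removal. Assume removal never lowers a score. The observed share is

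o = b + (1 − b) × a,

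so a = (o − b) / (1 − b), and the fraction of raised scores due to removal is (o − b) / o. With o = 20% (assumed):

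| b (assumed) | a | Fraction due to removal |
|---|---|---|
| 0% | 20.0% | 100% |
| 5% | 15.8% | 75% |
| 10% | 11.1% | 50% |
| 15% | 5.9% | 25% |
| 20% | 0% | 0% |

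The planned data are the same in all five rows. If removal had no effect and b were 5% to 20% (assumed), then 192 × 0.05 = 9.6 to 192 × 0.20 = 38.4 occasions would be counted as pain.

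**4. What the planned test can show.** This is a simulation with 1,000 runs, 48 infants and one score each. Pre-removal scores are binomial on 0 to 7, any rise is Poisson, totals are capped at 7, and tests are one-sided at 5%. All distributions are assumptions.

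| Pre-removal mean | Mean rise at removal | Planned test shows below 3 | Paired test shows a rise |
|---|---|---|---|
| 0.5 | 0 | 100% | 0% |
| 0.5 | 1.0 | 100% | 100% |
| 0.5 | 1.5 | 99.9% | 100% |
| 3.0 | 0 | 6.4% | 0% |
| 3.5 | 0 | 0% | 0% |

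The planned test gives the same favourable answer whether or not removal raised the score by 1.0 to 1.5 points. It also rarely or never gives that answer when infants were already near or above 3 and removal did nothing.

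**5. The cut-off.** The Outcomes section counts pain above 3, and the Statistical methods section counts it from 3 upward. A score of exactly 3 is pain under one and not under the other, so the reported count depends on which is used.

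**The case against.** The outcome can fairly be read as an absolute state, pain at the time of removal, and the planned analysis addresses exactly that. Background distress pushes scores up, so it works against a favourable result. If removal scores are low in infants able to respond, the data do show little pain at removal. This stands. A reader might infer that the pain question goes unanswered or that the scores are uninterpretable. The article does not support that reading, because the weakness appears only when scores are raised or rise below the cut-off.

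The mechanism also has limits. Breathing and arousal carry at most 1 point each, so together they give at most 2. Altered breathing from respiratory support cannot reach 3 without points for face, cry or limbs. Twelve of the 48 infants (subgroups A and C) are healthy and in room air. The 5% to 20% resting rate and the simulated distributions are assumptions, and a rise from 0.5 to 2.0 stays under the study's own threshold. The planned test is therefore not faulty; it answers a different question.

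A reader might also infer that a pre-removal score would settle attribution completely. It would not. An infant who responds little scores low both times, and handling between the two scores is part of the change.

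Finally, the data collection form is not shown and could contain a pre-removal field, and hourly forms and live annotations give some context. They do not supply a baseline NIPS, and the analysis as written would not use one.

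**Conclusion.** The concern holds in a limited form. As described, NIPS is measured once per removal and analysed as an absolute value, although its stated purpose is causal and the companion skin score is analysed as a change. Raised scores, and rises that stay below the cut-off, cannot be attributed to adhesive removal rather than to distress already present. Low scores remain informative.

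The size cannot be fixed from the article. On the assumed figures above, anything from none to all of the raised scores could be due to removal, and about 10 to 38 of 192 occasions could be counted as pain with no sensor effect. The structural conclusion does not depend on those figures; it rests on the stated timing and the stated analysis.

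This is a worthwhile improvement to a single-centre study with a convenience sample. It does not invalidate the safety objective. The conflict over the cut-off needs no assumption: the two sections disagree.

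**What to change.** At each removal where the researcher scores NIPS, have the same researcher also score it immediately before touching the sensor. Report the paired change, summarised per infant because each infant has repeated removals, and the number newly crossing the cut-off. Keep the planned post-removal average, count and test alongside.

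Reconcile the definition of a pain score between the Outcomes and Statistical methods sections and use one cut-off throughout, for the count, the number newly crossing and the test.

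The cost is one short extra observation and one form field per attended removal. Phase 2 includes periods with no study staff on site, so some replacements may have neither score; report how many. The paired change will not resolve blunted response and will not fully separate adhesive pain from handling at the same moment, and the report should say so. A pre-removal score cannot be recovered afterwards, so the change helps only removals still to come.
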